**Methods and analysis:**

This randomized, prospective, parallel-group clinical trial will include 52 patients (NYHA II–III) allocated into CRT (60–80% 1RM) or BFRRT (20–30% 1RM, calibrated at 50% arterial occlusion pressure) groups. The supervised intervention lasts 4 months, with an 8-month post-intervention follow-up. The primary outcome is the change in serum NT-proBNP levels. Secondary outcomes include quality of life, echocardiographic ventricular function, functional capacity, and clinical events. Advanced statistical models and exploratory machine learning analyses with k-fold cross-validation will be utilized for predictive modeling and exploring personalized medicine strategies.

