**Implications:**

The REHAB-WASHOUT HF trial aims to establish an effective, safe, and accessible therapeutic approach for HF rehabilitation, potentially enhancing clinical outcomes and guiding personalized prescriptive strategies in cardiovascular rehabilitation.

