#### Statistical analysis and machine learning plan

2.5.21

All primary and secondary clinical, functional, and biochemical outcome analyses will be conducted strictly based on the intention-to-treat principle. Accordingly, all randomized participants will be evaluated within their originally allocated treatment groups, regardless of compliance, session attendance, missing data, or subsequent protocol deviations. Continuous variables will be presented as mean plus or minus standard deviation for data with a normal distribution, or as median and interquartile range for non-normally distributed data.

Categorical variables will be expressed as absolute frequencies and percentages and will be compared utilizing the chi-square test. Continuous variables demonstrating normal distribution will be analyzed using analysis of covariance models, adjusted for age and sex as clinical baseline covariates. The essential prerequisites for the analysis of covariance models—including linearity, normality of distribution, and homogeneity of variance—will be strictly verified through visual inspection of histograms, normal probability plots, and residual scatter plots.

Continuous variables with non-normal distribution will undergo logarithmic transformation to correct distribution asymmetry. If normal distribution is not achieved following transformation, generalized linear models or robust statistical methods will be applied to guarantee appropriate adjustments for age and sex. All classical statistical analyses will be conducted utilizing the R Studio environment (version 1.12, R language version 4.2).

In addition to traditional frequentist statistical analyses, advanced machine learning and artificial intelligence techniques will be deployed to optimize data interpretation and discover predictive biomarkers of therapeutic response to the physical exercise interventions. To predict individual clinical responses to the cardiovascular rehabilitation protocol—specifically changes in N-terminal pro-brain natriuretic peptide, peak oxygen consumption, and quality of life scores—supervised learning algorithms will be implemented, including random forest, gradient boosting machines, and support vector machines. To mitigate the risk of model overfitting and ensure generalizability, these supervised algorithms will be evaluated using a k-fold cross-validation strategy.

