Unsupervised learning methods, specifically k-means and hierarchical clustering algorithms, will be utilized to perform clinical phenotyping of patient subgroups based on multidimensional profiles incorporating baseline inflammatory, functional, and echocardiographic variables. Feature selection and model interpretability will be enhanced using least absolute shrinkage and selection operator regression alongside Shapley Additive exPlanations values to identify and rank the most relevant predictive clinical variables. Longitudinal data tracking dynamic trajectories of clinical response over time will be comprehensively analyzed using mixed-effects models and, where applicable, recurrent neural networks.

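### The ranking of predictors of each patient's own change cannot separate prognostic markers from markers that alter the BFRRT-versus-CRT difference, yet its output is called predictive and the article speaks of personalised prescription

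*Protocol article*

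**What the plan says.** Section 2.5.21 of the protocol article (Statistical analysis and machine learning plan) gives the aim of the machine-learning work as to "discover predictive biomarkers of therapeutic response to the physical exercise interventions". The task is stated as "To predict individual clinical responses to the cardiovascular rehabilitation protocol", and the targets are "changes in N-terminal pro-brain natriuretic peptide, peak oxygen consumption, and quality of life scores". On method, "supervised learning algorithms will be implemented, including random forest, gradient boosting machines, and support vector machines". LASSO regression and SHAP values are then used "to identify and rank the most relevant predictive clinical variables". Mixed-effects models, and recurrent neural networks where applicable, are named for trajectories over time.

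The section names no arm-by-marker term, no separate fits by arm and no model of the treatment difference. It lists no input variables for the supervised learners, so it does not say whether randomised arm is one of them. The classical part uses "analysis of covariance models, adjusted for age and sex as clinical baseline covariates".

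The abstract (Methods and analysis) calls the machine-learning work exploratory and gives its purpose as "predictive modeling and exploring personalized medicine strategies". The abstract (Implications) says that the trial as a whole may contribute to "guiding personalized prescriptive strategies in cardiovascular rehabilitation". Section 2.5.3 randomises 1:1 between CRT and BFRRT, and there is no untrained arm.

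**The concern.** With two trained arms and no untrained control, the prescription question that randomisation can answer is which patients do better on BFRRT and which on CRT. A marker bears on that only if the between-arm difference varies with it. A marker that tracks change equally in both arms is prognostic: it says who will improve, not which programme to choose.

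The target stated in section 2.5.21 is the patient's own change, and the selection tool ranks whatever predicts that change. The output is nevertheless called predictive of therapeutic response, and the article speaks of personalised prescription. A prognostic marker could therefore be reported as a guide to choosing the programme, and a real effect modifier could be passed over.

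**Working it through.** **Inputs.** Section 2.2 gives 24 patients per group before attrition, an effect size of 0.83, two-sided alpha 0.05 and 80% power. The machine-learning section gives no figures of its own. The marker slopes and marker prevalence below are assumptions.

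**The plan's own figure.** (73 - 15)/70 = 58/70 = 0.83; with the pooled SD √((68² + 70²)/2) = 69.0 it is 0.84. For d = 0.83 the two-sample t test needs 23.8, so 24 per group (power 80.4%). This reproduces, and gives 2 × 24 = 48 analysed patients.

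**What each analysis sees.** Let y = 0.83·arm + b(arm)·x + error, with error SD 1, x standard normal and arm = 1 for BFRRT. With equal allocation:
- a model of change on x estimates the average slope, (b_CRT + b_BFRRT)/2;
- the arm-by-marker term estimates the slope difference, b_BFRRT - b_CRT.

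Only the second bears on the choice of programme, because the arm difference at x is 0.83 + (b_BFRRT - b_CRT)·x.

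**Simulation, n = 48, at least 5,000 runs per row, percentage significant at 0.05:**

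| Slopes CRT / BFRRT | Average slope | Slope difference | Pooled test | Arm-by-marker test |
|---|---|---|---|---|
| 0.3 / 0.3 | 0.3 | 0 | about 46 | 5 |
| 0.5 / 0.5 | 0.5 | 0 | about 86 | 5 |
| -0.3 / 0.3 | 0 | 0.6 | about 6 | 49 |
| -0.5 / 0.5 | 0 | 1.0 | about 7 | 88 |
| -0.2 / 0.8 | 0.3 | 1.0 | about 39 | 88 |
| 0 / 1 | 0.5 | 1.0 | about 78 | 88 |
| 0.2 / 1.2 | 0.7 | 1.0 | about 96 | 88 |
| 0 / 0.5 | 0.25 | 0.5 | 33 to 34 | 36 to 38 |

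The four rows with a slope difference of 1.0 imply the same reversal: BFRRT is the worse choice when 0.83 + 1.0·x < 0, that is x < -0.83, about 20% of patients. The pooled test flags them in anything from 7% to 96% of runs, depending only on the average slope. It flags the 0.5 / 0.5 marker, which carries no information about choice, in 86%.

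**Arm added as a main effect only.** The pooled figures become about 90% for 0.5 / 0.5 and 7% for -0.5 / 0.5, so adjustment for arm does not separate the two kinds of marker.

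**Random forest.** Marker A is prognostic only (0.5 SD per SD). Marker B changes the arm difference by 0.83 SD per SD and has no average effect. Permutation importance:
- arm not a feature: B about 0 at both 48 and 2,000 patients;
- arm a feature, 48 patients: B 0.02, A 0.20;
- arm a feature, 2,000 patients: B 0.20, A 0.32.

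With arm included, the forest can pick B up, but the rank does not show which of the two modifies the effect.

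**Power of the remedy.** For a 50/50 binary marker the interaction has SE = 4·SD/√N = 4/√48 = 0.577 SD. An interaction of 0.83 SD gives 0.83/0.577 = 1.44 and power of 29% (t) or 30% (normal). For 80% power, N = 16·((1.96 + 0.84)/0.83)² = 182.3, so about 183 analysed patients.

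**The case against.** The strongest reply is that the article lists no inputs for the learners. Silence about arm does not show that arm is left out: the ANCOVA sentence names only age and sex, and nobody would conclude that it omits the group term. Input lists and interaction terms are details that a condensed article may leave to the full plan. This stands. A reader might infer that the arms are pooled without regard to allocation and that randomisation is discarded; the text does not establish that. What remains is stated in the article itself: the target is own change, the tool is a ranking of its predictors, and the label and purpose go further. That mismatch is present whether or not arm is an input.

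Second, the prescription wording is a hedged hope for the whole trial, not the learners' declared estimand, and the machine-learning work is labelled exploratory. This also stands, and it limits the weight of the point. An exploratory label covers uncertainty about a result, though, not a label that names a different quantity.

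Third, a reader might infer that effect modifiers always cancel out in a model of change, or that only markers with opposite effects in the two arms can reverse the choice. Neither is true: slopes of 0 / 1 or 0.2 / 1.2 give the same reversal and are often flagged. The near-chance detection is special to modifiers whose average slope is close to zero.

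Fourth, the 88% for the interaction test needs a slope difference of 1.0 SD per SD, larger than the planned main effect of 0.83. At slopes 0 / 0.5 it does hardly better than the pooled test. The case for it is that it asks the right question, not that it is powerful at this sample size.

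**Conclusion.** The point holds as a mismatch between target and label in an exploratory analysis. Ranking predictors of own change does not separate prognostic from effect-modifying markers, and it can miss a modifier with an average effect near zero. The illustration (86% against 5% for a purely prognostic marker; 7% against 88% for an exactly symmetric modifier) rests on assumed slopes, 48 patients, and a linear test in place of LASSO, forests, boosting and support vector machines. It shows the direction of the problem, not the error rate of the planned learners.

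The documents do not show that arm is excluded, and no null hypothesis is stated for this work. The primary and secondary comparisons do not depend on it.

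**What to change.** In section 2.5.21, for the exploratory analyses:
- Include randomised arm and arm-by-candidate terms in the LASSO and mixed-effects models. Where a mixed model uses repeated values rather than change, the relevant term is arm by candidate by time.
- For the tree-based and support vector models, predict the BFRRT-minus-CRT difference for each patient, by separate fits in each arm or an equivalent method, and rank variables on that difference.
- Reserve the terms predictive and prescriptive for variables with interaction support, and call the rest prognostic.
- In the abstract, limit the personalised-prescription wording to interaction results and call them hypothesis-generating.

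If only prognostic modelling is intended, relabelling the output and narrowing the abstract would be enough.

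The cost is a few lines of text and code on data already planned. The real downside is low power: about 30% for a 50/50 binary marker with a 0.83 SD interaction at 48 patients, so few markers will be supported.

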### Sample size calculation

2.2

The sample size calculation was informed by the data reported by Tanaka et al. [13], who evaluated a BFR-based exercise protocol in patients with HF (New York Heart Association [NYHA] functional class I or II). In their trial, a post-training reduction in brain natriuretic peptide (BNP) of 73 ± 68 pg/mL was observed in the BFR group, compared to a reduction of 15 ± 70 pg/mL in the conventional CR control group [13].

Based on these values, a Cohen's *d* effect size of 0.83 was calculated. Assuming a 1:1 allocation ratio between the experimental arms, a minimum of 24 patients per group is required to achieve a statistical power of 80% with a two-tailed alpha level of 0.05. To account for an anticipated attrition rate of approximately 10%, the final sample size has been established at 26 patients per treatment arm, resulting in a total target recruitment of 52 participants. BNP data from Tanaka et al. were used as the closest available proxy because both biomarkers reflect cardiac wall stress and no directly comparable BFR exercise trial reporting NT-proBNP was available, although this trial will evaluate N-terminal pro-brain natriuretic peptide (NT-proBNP) as its primary biochemical outcome.

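### Change from baseline is read as individual therapeutic response, and k-fold cross-validation is credited with generalizability that it cannot give in 52 patients at one centre

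*Protocol article*

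**What the plan says.** Section 2.5.21 (Statistical analysis and machine learning plan) of the protocol article sets out random forest, gradient boosting and support vector machines to predict individual clinical response to rehabilitation. It defines response as "specifically changes in N-terminal pro-brain natriuretic peptide, peak oxygen consumption, and quality of life scores". The declared purpose is to find biomarkers that predict response to the exercise interventions.

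On validation it says: "To mitigate the risk of model overfitting and ensure generalizability, these supervised algorithms will be evaluated using a k-fold cross-validation strategy".

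On ranking predictors it says: "Feature selection and model interpretability will be enhanced using least absolute shrinkage and selection operator regression", together with Shapley values.

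Three other places matter:
- **Sample.** Section 2.2: "the final sample size has been established at 26 patients per treatment arm, resulting in a total target recruitment of 52 participants".
- **Design.** Section 2.1 describes a single-centre trial of two exercise programmes. There is no untrained arm.
- **Features and status.** Section 2.5.18 gives the biochemical panel, NT-proBNP included, a role as baseline covariates. The Abstract labels the machine-learning work exploratory.

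**The concern.** Two statements in section 2.5.21 are open to correction whatever a fuller analysis plan may add.

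**The validation claim.** Cross-validation reuses the same patients, recruited, trained and measured at one centre. It estimates how a model performs on further patients drawn from that same source. It carries no information about other centres, assays or case mix.

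**Change equated with response.** A patient whose baseline value is high partly by chance will tend to fall at follow-up whatever the treatment does. Baseline therefore predicts change even when every patient responds identically. Cross-validation guards against fitting noise that does not recur in held-out patients. Regression to the mean does recur, so it counts as genuine predictive skill. Since both arms train, nothing in the design separates this drift from the effect of exercise in an individual patient.

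At stake is the aim of guiding personalised prescription. A baseline value, or a marker that merely tracks it, could be reported as a predictor of who benefits, with a validation statement that the data cannot support.

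**Working it through.** **1. The sample size the models will have.** The article gives no figure for the machine-learning part, so the only figure to reproduce is n. From section 2.2, d = (73 − 15)/70 = 0.829, which matches "a Cohen's *d* effect size of 0.83 was calculated". A two-sided t-test at alpha 0.05 with 80% power needs 23.8, so 24 per arm (power at 24 is 0.804). Recruitment is 2 × 26 = 52. If 24 per arm complete, 48 remain.

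**2. How much of change is explained by baseline when nobody responds differently.** Let Y0 and Y1 be the baseline and week-16 values, with equal variance σ², correlation r, and the same treatment effect for all.
- Cov(Y1 − Y0, Y0) = rσ² − σ² = −(1 − r)σ²
- Var(Y1 − Y0) = 2(1 − r)σ²
- Correlation = −(1 − r)/√(2(1 − r)) = −√((1 − r)/2)
- Share of variance explained = (1 − r)/2

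**3. Does 5-fold cross-validation remove it?** Change was regressed on baseline alone in simulated trials of 52 patients with a homogeneous effect (2,000 runs per row). R² is measured against the training-fold mean. The correlation r is an assumption throughout.

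| r | corr(change, baseline) | (1−r)/2 | mean 5-fold R² | central 95% of runs | R² above zero |
|---|---|---|---|---|---|
| 0.6 | −0.447 | 0.20 | 0.169 | −0.02 to 0.40 | 96% |
| 0.7 | −0.387 | 0.15 | 0.121 | −0.05 to 0.33 | 90% |
| 0.8 | −0.316 | 0.10 | 0.072 | −0.07 to 0.27 | 78% |
| 0.9 | −0.224 | 0.05 | 0.024 | −0.10 to 0.19 | 58% |

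With 48 patients the means are 0.170, 0.120, 0.069 and 0.020. If R² is measured against the overall mean of the outcome, a stricter convention, the means fall to about 0.13, 0.08, 0.03 and −0.02. R² is then above zero in 88%, 76% and 60% of runs at r = 0.6, 0.7 and 0.8. The artefact survives cross-validation except when r is high.

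**4. Would a ranking pick it up?** A random forest was fitted to change with 20 features: baseline value, arm and 18 noise variables (60 runs per r). Chance alone would put any one feature first in 1/20 = 5% of runs. Baseline came first in 52%, 47% and 25% of runs at r = 0.7, 0.8 and 0.9.

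**5. What the remedy does.** Here the target is the week-16 value and the reference model is baseline value plus arm. A pure-noise marker added to the reference gives a mean cross-validated gain of −0.029, −0.027 and −0.025 at r = 0.7, 0.8 and 0.9 (1,000 runs each). Regression to the mean is absorbed by the reference and no longer counts as discovery. The noise marker still shows a positive gain in 21% to 23% of runs, so a small positive gain from a single split is not evidence.

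**The case against.** The strongest reply has four parts.

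**The target is not in itself an error.** In an unpenalised linear model that contains the baseline value, modelling change or modelling the week-16 value gives the same coefficient for every other predictor. Only the baseline coefficient and R² differ. That is correct. It does not carry over exactly to penalised or tree-based models, and R² and feature rankings are what this plan would report. What remains is a problem of interpretation and of the missing comparison with baseline plus arm.

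**The artefact is not certain.** A reader might infer that the analysis is bound to report regression to the mean as biomarkers. The article does not say that each target's baseline value will be a feature. Section 2.5.18 makes this likely for NT-proBNP, but its reference to covariates could equally mean adjustment. The size also depends on r, and at 0.9 it is small. So the claim is that the analysis can mislead in this way.

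**Other tempting charges lack support.**
- A reader might take the targets to be untransformed differences. The article says only that they are changes, and log-transforms skewed variables elsewhere in the section. The algebra in step 2 applies on either scale.
- A reader might suspect that feature selection is done before the folds are formed. The article does not say so, and nesting, tuning and the choice of k are details that a fuller plan commonly holds.
- A reader might want the neural network struck out because Table 1 has only three assessment times. The text reads "mixed-effects models and, where applicable, recurrent neural networks", and that condition lets the team leave it out.

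**The work is exploratory.** The Abstract says so, and the randomised comparison of NT-proBNP is untouched. This limits the seriousness. It does not make the generalizability statement true.

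**Conclusion.** The point holds in a limited form. The statement that k-fold cross-validation secures generalizability is wrong for a single-centre sample of 52 and needs correcting whatever else is planned. Treating change as individual response is unsafe, because cross-validation leaves regression to the mean in place. With no true responders, baseline accounts for 5% to 20% of the variance in change over r = 0.9 to 0.6, and the mean 5-fold R² is about 0.02 to 0.17.

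These sizes rest on four assumptions: an r that the article does not give, equal variances at the two times, a homogeneous treatment effect, and baseline values or their correlates among the features. The consequence is confined to the exploratory biomarker claims. The primary analysis, sample size and safety assessments are not affected. It should be changed, but it does not threaten the trial's main result.

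**What to change.** In section 2.5.21:
1. Make the week-16 value the target for each of the three outcomes, with its baseline value and arm in every model.
2. Define a reference model with baseline value and arm only, and report each model's cross-validated gain over it, with its uncertainty.
3. Describe a variable as predictive of response to one training type over the other only on the basis of an arm-by-variable term, reported as exploratory.
4. Replace the claim of ensured generalizability with the statement that cross-validation will *estimate internal predictive performance*.

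The cost is analysis wording and some computing time; no extra patients or visits are needed. Reported performance will look less favourable. Arm-by-variable terms will also be imprecise. For a marker that splits each arm of 26 evenly into 13 and 13, the interaction has a standard error of √(4/13) = 0.555 SD, against √(2/26) = 0.277 SD for the arm comparison. That is the reason to keep them exploratory.

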## Ethical compliance

The study protocol was reviewed and approved by the Research Ethics Committee of the Catholic University of Brasília (CAAE: 64955022.9.1001.0029). All procedures were conducted in accordance with the ethical principles outlined in the Declaration of Helsinki. Written informed consent was obtained from all participants prior to their inclusion in the study.

## Declaration of generative AI and AI-assisted technologies in the manuscript preparation process

During the preparation of this work the author(s) used Gemini (Google) in order to improve the English language, technical terminology, and manuscript formatting. After using this tool/service, the author(s) reviewed and edited the content as needed and take(s) full responsibility for the content of the published article.

